## Abstract

**Background:**

Along with the marked increase in early gastric cancer (EGC) in the Eastern countries, there has been an effort to adopt the sentinel node concept in EGC to preserve gastric function and reduce the occurrence of postoperative complications. Based on promising results from a previous quality control study, this prospective multicenter randomized controlled phase III clinical trial aims to elucidate the oncologic safety of laparoscopic stomach-preserving surgery with sentinel basin dissection (SBD) compared to a standard laparoscopic gastrectomy.

**Methods/Design:**

This trial is an investigator-initiated, open-label, multicenter randomized controlled phase III trial with a non-inferiority design. Patients diagnosed with a single lesion of clinical stage T1N0M0 gastric adenocarcinoma, with a diameter of 3 cm or less are eligible for the present study. A total of 580 patients (290 per group) will be randomized to either laparoscopic stomach-preserving surgery with SBD or standard surgery. The primary end-point is 3-year disease-free survival (DFS) and the secondary endpoints include postoperative morbidity and mortality, quality of life, 5-year DFS, and overall survival. Qualified investigators who completed the prior quality control study are exclusively allowed to participate in this phase III clinical trial.

**Discussion:**

The proposed trial is expected to verify whether laparoscopic stomach-preserving surgery with SBD achieves similar oncologic outcomes and improved quality of life compared to a standard gastrectomy in EGC patients.

**Trial registration:**

This study was registered at the NIH ClinicalTrial.gov database (NCT01804998) on March 4th, 2013.

## Background

Gastrectomy with extended lymph node dissection has long been considered a standard treatment for gastric cancer to ensure satisfactory long-term survival [1]. As nodal metastasis has a great influence on disease prognosis following curative treatment for gastric cancer, the complete eradication of potential metastatic nodes is essential to reduce loco-regional recurrence and achieve optimal oncologic outcomes.

However, some investigators question whether the standard treatment can be excessive in certain populations with early-stage disease where prophylactic lymph node dissection might play a minor role in terms of curing the disease. The prevalence of lymph node metastasis in early gastric cancer (EGC) is reported to be in the range of 7.7 to 19.4 % [2–4], which means that the remainder of patients are free of nodal metastasis and may unnecessarily undergo an extensive lymphadenectomy at the expense of their quality of life (QOL).

The sentinel node (SN) is defined as the first lymph node to receive lymphatic drainage from the primary tumor, and lymph node metastasis is assumed to initially occur at this site. Many investigators have demonstrated that metastasis via the lymphatic channel occurs in a stepwise manner in malignant melanoma and breast cancer, and SNs can represent the overall metastatic status of the lymph nodes [5, 6]. The accuracy of a sentinel lymph node biopsy is reported to extend over 95 % in breast cancer and melanoma [7–9], and this result provides supporting evidence to obviate unnecessary lymphadenectomy in those with negative SNs, which consequently leads to less frequent postoperative morbidity and improved QOL in patients with breast cancer or malignant melanoma [10–12].

There has been consistent effort over the last decade to apply the SN concept in gastric cancer. As the standard gastrectomy with lymphadenectomy can induce unwanted surgical complications, as well as, long-term nutritional and functional deficits, SN navigation surgery is expected to provide a better QOL in gastric cancer patients by reducing the extent of the surgery with respect to lymph node dissection and gastric resection. However, the clinical application of SN biopsy in gastric cancer has been challenging due to the complicated nature of multidirectional lymphatic drainage in the stomach, and the possibility of skip metastasis [13–15].

Nonetheless, the details of the procedure have gradually evolved, to improve the outcomes of SN detection and evaluation in gastric cancer patients, through trial and error [16]. A recently published multicenter study from Japan demonstrated promising results in terms of the feasibility of SN navigation surgery in gastric cancer patients [17]. However, it is yet to be adopted as routine clinical practice owing to insufficient evidence of oncologic safety compared to conventional surgery.

Therefore, we herein propose a randomized controlled clinical trial (SEntinel Node ORIented Tailored Approach [SENORITA] trial) to elucidate whether stomach-preserving surgery with sentinel basin dissection (SBD) achieves a similar disease-free survival (DFS) rate as the standard gastrectomy, as well as, the impact on postoperative morbidity, mortality, and QOL in patients with EGC.

## Methods/Design

### Study design

The SENORITA trial is an investigator-initiated, open-labeled, parallel-assigned, multicenter randomized controlled phase III trial. It is schematically described in Fig. 1. This study will involve 7 medical institutions (National Cancer Center, Gyeongsang National University Hospital, Ajou University Hospital, Dongnam Institute of Radiological and Medical Science, Yonsei University Severance Hospital, Soonchunhyang University Bucheon Hospital, and Chonnam National University Hwasun Hospital), which have been qualified to participate in this phase III trial following completion of the prior quality control study (NCT01544413) [18, 19].

**Fig. 1 Fig1:**
[figure not shown]
Study scheme of SENORITA trial, inclusion and exclusion criteria, intervention, and end points (EGJ, esophagogastric junction; EGD, esophagogastroduodenoscopy; CT, computed tomography; EUS, endoscopic ultrasonography; LND, lymph node dissection; SBD, sentinel basin dissection; SBN, sentinel basin node; ESD, endoscopic submucosal dissection; EFTR, endoscopic full-thickness resection; LWR, laparoscopic wedge resection; LSR, laparoscopic segmental resection; DFS, disease-free survival; OS, overall survival)

The institutional review board (IRB) of the National Cancer Center, Korea has approved this study (IRB No. NCCCTS-13-661). The study has also been approved by the local ethical committee of each participating center (Gyeongsang National University Hospital [2013-06-002], Ajou University Hospital [AJIRB-MED-OBS-13-338], Dongnam Institute of Radiological and Medical Science [D-1304-002-001], Yonsei University Hospital [4-2013-0491], Soonchunhyang University Bucheon Hospital [SCHBC 2013-01-099], and Chonnam National University Hwasun Hospital [CNUHH-2014-051]). Written informed consent will be obtained from all patients prior to patient recruitment. The trial has been registered in the database of clinical trials (NCT01804998). An independent data monitoring committee (IDMC), which is separately organized by independent experts who are not participating in this study, will monitor the clinical trial; the IDMC consists of a surgeon, a gastroenterologist, and a statistician.

### Study population & eligibility criteria

The patient inclusion and exclusion criteria are as follows:

#### The following patients were included in the study

i.Patients with a single lesion of histologically confirmed adenocarcinoma in the stomach in preoperative endoscopic biopsyii.Patients with clinical stage of T1N0M0 gastric cancer according to the American Joint Committee for Cancer (AJCC) 7^th^ edition [20] (determined by preoperative endoscopy and computed tomography and/or endoscopic ultrasound)iii.Patients with a gastric cancer of less than 3 cm as the longest diameteriv.Patients with a gastric cancer at least 2 cm apart from the pylorus or the cardiav.Patients who plan to undergo laparoscopic surgeryvi.Patients aged > 20 and < 80 yearsvii.Patients with an Eastern Cooperative Oncology Group (ECOG) performance status of 0 or 1viii.Patients who agree to participate in the clinical study through informed consent

#### The following individuals were excluded from the study

i.Patients with a lesion satisfying the absolute indications of endoscopic resection (<2 cm, mucosal lesion, differentiated type)ii.Patients who are not indicated for surgical treatment due to serious cardiovascular or pulmonary diseaseiii.Pregnant womeniv.Patients with a past history of drug-related anaphylactic reaction, prior upper abdominal surgery (except for laparoscopic cholecystectomy) or radiation therapyv.Patients diagnosed with other malignancy within 5 years

### Randomization & allocation

The web-based clinical trial management system (eVelos System; Velos, Inc., Fremont, CA: http://eresearch.ncc.re.kr/velos/jsp/ereslogin.jsp) at the Clinical Research Coordination Center (CRCC) within the National Cancer Center, Korea, will coordinate the study and handle the data analysis. As soon as written informed consent is obtained from the eligible patient, the patient will be registered in the system and randomly allocated to one of the two surgical groups: laparoscopic SBD with stomach preserving surgery or standard laparoscopic gastrectomy with D1+ or more lymphadenectomy according to the Japanese gastric cancer treatment guidelines [1]. To reduce potential bias and confounding, participants will be further stratified based on the institution where the procedure is performed, depth of tumor invasion (mucosa vs. submucosa), and size (≤2 cm vs. > 2 cm) of the primary tumor. The random block size permutation method was used to generate the initial randomization sequence, and the randomization task will be centrally coordinated by the CRCC.

All registered patients will undergo a routine preoperative evaluation, including full laboratory tests, electrocardiogram, chest X-ray, pulmonary function test, and assessment for tumor markers.

### Intervention

#### Experimental group

##### Procedures for SBD

A detailed description of the SBD procedure is provided in our preceding report on the quality control study for the SENORITA trial [19]. Briefly, a mixture of indocyanine green (IGC; Diagnogreen®, Daiichi-Sankyo Co., Ltd., Japan; 2 mL, 5 mg) and radiolabeled human serum albumin (Tc99m-HSA; 2 mL, 0.1 mCi/mL) is used as a tracer to detect the SNs. The tracer is uniformly prepared at the reference center and delivered to the participating institutions. A 4-mL volume of the dual tracer is injected into the submucosal layer in 4 quadrants of the primary tumor via an intraoperative endoscopic approach. After 15 min of the endoscopic tracer injection, the sentinel basins containing SNs (green or hot) are carefully dissected and retrieved from the surgical field.

The harvested sentinel basins are then dissected to isolate lymph nodes, whilst in the operating room. All the isolated lymph nodes from the sentinel basins, defined as sentinel basin nodes (SBN), are classified into hot nodes (HN: radioactive nodes), green nodes (GN: stained nodes), both hot and green nodes (HGN), and basin nodes (BN: nodes within the sentinel basins, but neither hot nor green), labeled with the respective lymph node station numbers, and sent to the pathologist for intraoperative frozen section evaluation.

##### Intraoperative & postoperative pathologic evaluation

The harvested nodes from the sentinel basins are histologically examined intraoperatively with hematoxylin and eosin (H&E) staining using 1 representative cut plane of a frozen section for lymph nodes less than 4 mm. For nodes thicker than 4 mm, a slice will be made at a 2-mm interval parallel to the long axis so as not to miss macrometastasis. If all the harvested SBNs are tumor-free, stomach-preserving primary tumor resection is then carried out in accordance with the suggested procedure in the previous publication [4]. The detailed methods of primary tumor control are shown in Table 1. The resection margins of the specimen containing the primary tumor will be intraoperatively evaluated with frozen section examination as well; and patients with margin involvement will undergo further resection to achieve negative margins, or be converted to the standard surgery depending on the intraoperatively measured tumor size and margin status. However, specimens from the endoscopic resection will be reserved for permanent pathology.

**Table 1 Tab1:** Recommended methods of primary tumor control in the SENORITA trial

	Mucosa		Submucosa	
	≤20 mm	21–30 mm	≤20 mm	21–30 mm
Differentiated type	Exclusion	ESD or LWR/EFTR or LSR	LWR/EFTR or LSR	LSR
Undifferentiated type	ESD or LWR/EFTR or LSR	LSR	LWR/EFTR or LSR	LSR

*ESD* endoscopic submucosal dissection, *LWR* laparoscopic wedge resection, *EFTR* endoscopic full-thickness resection, *LSR* laparoscopic segmental resection

After the surgery, those SBNs proven tumor-free in the intraoperative frozen section examination will be re-evaluated. For permanent histologic evaluation, 1 section of the paraffin-embedded SBNs is stained with H&E and cytokeratin immunohistochemistry (IHC). The nodes are further examined with H&E stains for 3 deeper step sections at 200-μm intervals. When the intraoperative report is proven to be a false negative, or the SBNs are found by way of enhanced procedures to have intraoperatively unnoticed macrometastasis in the paraffin-embedded sections, the patient will be designated to undergo reoperation with the standard surgery. Conversely, watchful observation will be prescribed for patients with micrometastasis or isolated tumor cells (ITC) only in paraffin-embedded sections.

Meanwhile, in cases where macro- or micrometastasis is detected in the frozen sections during intraoperative pathologic examination, the surgery will be converted immediately to a standard gastrectomy with lymphadenectomy, as suggested in the Japanese gastric cancer treatment guidelines.[1]

#### Control group

The patients allocated to the control group will undergo standard laparoscopic gastrectomy, which includes laparoscopic distal gastrectomy, laparoscopic total gastrectomy, laparoscopic proximal gastrectomy, and laparoscopic pylorus-preserving gastrectomy, with D1+ or more lymphadenectomy [1].

### Postoperative follow-up schedule

All patients enrolled in this trial will be followed up regularly at stated intervals after the surgery. During the follow-up visits, patients will undergo laboratory tests, endoscopy, abdominal computed tomography, and QOL evaluation as described in Table 2.

**Table 2 Tab2:** Summary of the follow-up visit schedule and assessed parameters at each time point

	Preoperative	1 M	3 M	6 M	12 M	18 M	24Y	30 M	36 M	42 M	48 M	54 M	60 M
EGD	*			*	*	*	*	*	*		*		*
CT	*			*	*	*	*	*	*		*		*
Laboratory	*	*	*	*	*	*	*	*	*	*	*	*	*
QOL	*		*		*		*		*				

*EGD* esophagogastroduodenoscopy, *CT* computed tomography, *QOL* quality of life

* Evaluation at the desginated time point

### Outcome measurement

#### Primary outcome

The primary endpoint of the SENORITA trial is 3-year DFS of laparoscopic stomach-preserving surgery with SBD compared to that of conventional laparoscopic gastrectomy with lymphadenectomy in gastric cancer patients diagnosed as clinical stage T1N0M0. To assess DFS in this trial, the criteria for the event is as follows: recurrence of the primary tumor at resection margins, metachronous cancer development at the remnant stomach, histologically proven or radiologically apparent recurrence in the peritoneal cavity including intraabdominal lymph nodes, distant metastasis, newly developed malignancy in other organs, and other cause of death.

#### Secondary outcomes

The secondary endpoints of this trial include postoperative morbidity and mortality, QOL, and 5-year DFS and overall survival. Postoperative morbidity and mortality occurring within 30 days after the surgery will be reported and graded according to the modified Clavien-Dindo severity classification [21].

QOL will be assessed by the validated Korean version of the European Organization for Research and Treatment of Cancer (EORTC) questionnaires. The enrolled patients will be requested to fill out the core questionnaire (QLQ-C30) and the gastric cancer-specific module (QLQ-STO22) annually up to 3 years after the surgery [22, 23].

The trial will be assessed primarily based on the 3-year DFS. In the likelihood that the number of target events is insufficient for statistical analysis after the 3 years of follow-up, the 5-year DFS and overall survival will be reported as an alternative at the end of the study.

### Sample size calculation

The primary endpoint of this clinical trial is 3-year DFS of patients with gastric cancer of clinical stage T1N0M0. The required sample size was calculated based on a non-inferiority design assuming 97 % of patients achieve 3-year DFS following standard surgery. The margin of non-inferiority was 5 % and type 1 error was set at 0.05 with 80 % statistical power. As such, a sample size of 261 in each group with 24 target events is required. After considering a potential dropout rate of 10 % over the follow-up period, the final sample size is estimated as 290 patients in each study group (580 patients in total).

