### Interim analysis

When the number of events reaches 12 (50 % of the expected number of events), an interim analysis will be performed to identify any evidence of definite inferiority of the experimental intervention. The IDMC will subsequently evaluate whether the trial should be continued or terminated based on the results of the interim analysis.

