### Statistical analysis

Non-inferiority of the experimental study arm will be claimed if the lower confidence limit of 3-year DFS in the experimental study group exceeds 92 %. For survival analyses, the Cox proportional hazards model will be used. Kaplan-Meier curves will be used for survival curve estimation. Categorical variables will be analyzed by the Pearson’s *χ*^2^ test or Fisher’s exact test and continuous variables will be evaluated by the Student’s t-test or appropriate non-parametric method as required. The level of statistical significance will be set at 5 %.

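### The 24 target events and the 80 % power fit a hazard-ratio test, whereas the stated decision rule uses the experimental arm's 3-year DFS and has about 95 to 97 % power

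*Protocol article*

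**What the plan says.** All references are to the protocol article.

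- **Sample size calculation.** The design is non-inferiority, "assuming 97 % of patients achieve 3-year DFS following standard surgery". Then: "The margin of non-inferiority was 5 % and type 1 error was set at 0.05 with 80 % statistical power". The result is that "a sample size of 261 in each group with 24 target events is required". Allowing for "a potential dropout rate of 10 % over the follow-up period", this becomes 290 per arm. The section names no formula, no sidedness for alpha, and no time window over which the 24 events are counted.
- **Statistical analysis.** Non-inferiority is claimed if the "lower confidence limit of 3-year DFS in the experimental study group exceeds 92" %. The confidence level of that limit is not given. A Cox model is named for survival analyses in general, without a hazard-ratio margin and without a link to the non-inferiority claim.
- **Interim analysis.** The look takes place "When the number of events reaches 12", described as half of the expected number, so 24 is treated as the expected total.
- **Secondary outcomes.** "The trial will be assessed primarily based on the 3-year DFS". If target events prove too few after three years of follow-up, 5-year DFS and overall survival are to be reported instead.
- **Trial status.** Enrolment is expected to take 4 years, and patients are followed for 5 years.

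**The concern.** An event target is the currency of a log-rank or Cox test. A rule that compares one arm's 3-year DFS with a fixed 92 % needs no event target: its precision depends on the number of patients followed to three years. The sample size section and the decision rule therefore seem to describe different analyses, and a reader cannot tell which one the 80 % belongs to.

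This has practical consequences. The event target feeds two operational rules: the timing of the interim look, and the switch to 5-year DFS and overall survival. If the target does not match the 3-year endpoint, a trial in which both arms do as well as planned could be judged short of events and have its primary endpoint displaced, although the stated decision rule could still be applied.

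**Working it through.** **Inputs.** From Sample size calculation: control 3-year DFS 97 %, margin 5 points (so 92 % is the boundary), alpha 0.05, power 80 %, 261 per arm (522 in total), 290 per arm after dropout (580). From Trial status: 4 years of enrolment. Assumptions of this check: exponential DFS, uniform accrual, no loss to follow-up, and both arms truly at 97 %.

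**1. Reproducing the plan's figures.**
- Implied hazard-ratio margin: ln(0.92)/ln(0.97) = 2.737, with ln(2.737) = 1.007.
- Schoenfeld events, one-sided 5 %, 80 % power, 1:1: 4 × (1.645 + 0.842)² / 1.007² = 24.4. The plan says 24.
- Power at 24 events: Φ(√24/2 × 1.007 − 1.645) = 79 %. With 1.96 in place of 1.645 it is 69 %, and the requirement rises to 31 events.
- Dropout: 261/0.9 = 290. The plan says 290.

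So 24 events with 80 % power is a one-sided 5 % hazard-ratio calculation.

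**2. Power of the rule actually stated.** Treat 3-year DFS as a binomial proportion with 261 patients and an exact (Clopper-Pearson) lower limit.

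| Lower limit | Most events allowed for limit > 92 % | Power at true 97 % |
|---|---|---|
| one-sided 95 % | 13 of 261 | 97 % |
| one-sided 97.5 % | 12 of 261 | 95 % |

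If the sponsor meant a two-arm difference with a 5-point margin instead, the standard error is √(2 × 0.97 × 0.03 / 261) = 0.01493. The power is Φ(0.05/0.01493 − 1.645) = 96 %, or 92 % with 1.96. Neither version has 80 % power.

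**3. Events within three years of each patient's entry.**
- 522 × 0.03 = 15.7 and 580 × 0.03 = 17.4.
- Binomial chance of 24 or more: 2.8 % with 522 patients, 7.4 % with 580.
- A hazard-ratio test on 15.7 events would have 64 % power (one-sided 5 %).

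**4. Events if all follow-up counts.**
- Yearly hazard λ = −ln(0.97)/3 = 0.01015.
- With 4 years of uniform accrual and a data cut when the last patient reaches 3 years, the event probability is 1 − (e^(−3λ) − e^(−7λ))/(4λ) = 0.0494.
- 522 × 0.0494 = 25.8 and 580 × 0.0494 = 28.7.
- Chance of 24 or more: 67 % with 522 patients, 84 % with 580.

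**5. The interim fraction.** 12/24 = 50 %, as stated. Against the all-follow-up expectation it is 12/25.8 = 47 %. Against the 3-year count it is 12/15.7 = 77 %.

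**The case against.** The strongest reply is that nothing in the sample size section limits the 24 events to each patient's first three years. With 4 years of enrolment, most patients will have been observed for longer than that when the last one reaches three years. A Kaplan-Meier estimate at three years can coexist with a target that counts every DFS event. On that reading 24 is attainable and 12 is close to half. This stands. A reader might infer that 24 is an arithmetic error, that it cannot be reached, or that the interim look really falls at 77 % of the information. The document does not support any of these as a flat statement, because each depends on a cut at three years per patient that it does not specify.

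A reader might also infer that 24 and 261 were taken from two different formulas. Freedman's formula does give 261: 28.6 events / 0.055 / 2 = 260.07, rounded up. But a pooled two-proportion formula gives 257, and a Schoenfeld calculation with suitable accrual and loss inputs can also arrive at 261. No formula is named, so the origin of 261 stays open.

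Finally, a full protocol or analysis plan may hold the formula and the counting window, and their absence from an article is no fault. The mismatch itself is not an omission, however. The power, the event target, the decision rule, the interim trigger and the fallback are all stated here, and they do not describe one analysis. Counting all follow-up makes 24 reachable, but only by including events after a patient's third year. Those events serve a hazard-ratio test that the Statistical analysis section never sets up.

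**Conclusion.** The point holds as a mismatch between the sample size basis and the decision rule. The 24 events and 80 % power reproduce for a one-sided 5 % hazard-ratio test with margin 2.74. The stated rule on the experimental arm's 3-year DFS has about 97 % or 95 % power at 261 patients, depending on the confidence level, which is not given.

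It would be wrong to conclude that the trial is underpowered. Under the stated rule 80 % understates the power, and 290 per arm need not change.

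The event target matches 3-year DFS only loosely: about 16 events are expected within three years per patient, against about 26 over all follow-up. On the 3-year count, if too few events is taken to mean fewer than 24 (the article does not define it), the switch to 5-year DFS and overall survival would be likely even with both arms performing as planned. The chance of staying below 24 is then 97 % with 522 patients and 93 % with 580.

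The power of the stated rule rests on a true 97 % and complete three-year follow-up of 261 patients. The all-follow-up count rests also on exponential DFS and uniform 4-year accrual.

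**What to change.** Keep 290 per arm and reword four sections.

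1. **Statistical analysis and Sample size calculation.** Decide which rule settles non-inferiority, and state the confidence level, the sidedness of alpha and the power for that rule. With 261 evaluable per arm at 97 %:
   - single-arm limit above 92 %: about 97 % (one-sided 95 % exact limit) or 95 % (97.5 %);
   - two-arm difference below 5 points: about 96 % (one-sided 5 %) or 92 % (one-sided 2.5 %), by normal approximation;
   - hazard ratio below 2.74 with 24 events: about 79 % (one-sided 5 %) or 69 % (one-sided 2.5 %).
2. **Event target and Interim analysis.** Either tie the 24 events and the 12-event look explicitly to a hazard-ratio analysis over all follow-up, and say so in both sections. Or replace 24 with about 16 events expected within three years per patient, and correct the 50 % at the interim (12 of 15.7 is 77 %). Moving the look to another event count is not required by this point.
3. **Secondary outcomes.** State that the 3-year DFS analysis is carried out and reported whatever the number of events, with 5-year DFS and overall survival as additions and not as replacements.

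The cost is rewording only, with no change in patient numbers. It should be done before outcome data by arm are seen.
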